## Abstract

**Background:**

The use of physical restraints still is common practice in the nursing home care. Since physical restraints have been shown to be an ineffective and sometimes even hazardous measure, interventions are needed to reduce their usage. Several attempts have been made to reduce the use of physical restraints. Most studies used educational approaches and introduced a nurse specialist as a consultant. However, the success rate of these interventions has been inconsistent. We developed a new multi-component intervention (EXBELT) comprising an educational intervention for nursing home staff in combination with a policy change (belt use is prohibited by the nursing home management), availability of a nurse specialist and nursing home manager as consultants, and availability of alternative interventions. The first aim of this study is to further develop and test the effectiveness of EXBELT on belt restraint reduction in Dutch psychogeriatric nursing homes. However, the reduction of belts should not result in an increase of other restrictive restraints (such as a chair with locked tray table) or psychoactive drug use. The overall aim is an effective and feasible intervention that can be employed on a large scale in Dutch nursing homes.

**Methods and design:**

Effects of EXBELT will be studied in a quasi-experimental longitudinal study design. Alongside the effect evaluation, a process evaluation will be carried out in order to further develop EXBELT. Data regarding age, gender, use of physical restraints, the number of falls and fall related injuries, psychoactive drug use, and the use of alternative interventions will be collected at baseline and after four and eight months of follow-up. Data regarding the process evaluation will be gathered in a period of eight months between baseline and the last measurement. Furthermore, changing attitudes will become an important addition to the educational part of EXBELT.

**Discussion:**

A quasi-experimental study is presented to investigate the effects of EXBELT on the use of belts on wards in psychogeriatric nursing homes. The study will be conducted in 26 wards in 13 psychogeriatric nursing homes. We selected the wards in a manner that contamination between control- and intervention group is prevented.

**Trial registration:**

(NTR2140)

## Background

The use of physical restraints still is common practice in the nursing home care of older people with dementia. Physical restraints are defined as any limitation in an individual's freedom of movement [1] and includes those worn by the person (belt, chest, and arm/leg), those attached to beds (full-enclosure bedrails) or chairs (locked table). Although reports of restraint prevalence internationally varies from 15 to 66% [2,3], ranges of restraint prevalence in Dutch nursing homes is between 41 to 64% [2]. Recent prevalence measures in the Netherlands have shown that 10% to 14% of nursing home residents are restrained with belts [4,5].

Staff report that physical restraints are used to prevent falls [6-8]. The accumulating evidence that restraint reduction does not lead to an increased number of falls or fall-related injuries [9-11] and that restraint use can result in falls and problems with balance and coordination [6,12,13], call into question the continued use of these devices as "safety measures". Restraints have other known negative physical, psychological and social consequences for older persons. Both prolonged and short periods of physical restraint use are associated with pressure sores, loss of muscle strength and endurance, joint contractures, incontinence, demoralization, humiliation feelings of low self worth, depression, aggression and impaired social functioning [6,14,15]. Evans and colleagues [12] conducted a systematic review of physical restraint use in acute and residential health care facilities, and documented that the use of physical restraints (including belts), increases the risk of death, serious injury, as well as the length of hospital stay. Older adults report negative feelings about the restraint experience such as discomfort and indifference [16]. The use of restraints may also indicate a failure to address the real needs of the residents. Since physical restraints have been shown to be an ineffective and sometimes even hazardous measure, interventions are needed to reduce their usage.

Several attempts have been made to reduce restraint use in clinical practice [17-22]. Most interventions used educational approaches, aiming to improve nursing staff knowledge and confidence to avoid physical restraints and to use alternative measures that target the resident's underlying problems [18,19,21,22]. These intensive training sessions were delivered to staff by a nurse specialist provided to the nursing home as a consultant from the study team. The success rate of these interventions differs between countries; a successful educational intervention in the USA [18] proved to be ineffective in the Netherlands [19,23,24]. It is unclear whether these contradictory results can be explained by cultural differences, differences in health care systems, or difference in educational level of nursing staff in nursing homes between the USA and the Netherlands. The results of a recent study among Dutch, German and Swiss nursing staff indicate that opinions and attitudes towards physical restraints hinder attempts to reduce restraint use [25]. In this study, almost all nursing staff assessed the use of physical restraints in their clinical practice as appropriate. Moreover, Dutch nursing staff consistently assessed restraint measures as less restrictive than German and Swiss nursing staff and reported less discomfort in using restraints [25]. Furthermore, this and other studies indicate that the availability of alternative interventions is essential for effective restraint reduction [19,23-25]. For instance, in the study by Huizing and colleagues it was reported that the availability of some new and rather expensive alternative measures was limited [24]. Finally, there are indications that legislation influences the use of restraints; the success of the educational intervention in the USA has also been supported by a nursing home law that led to national nursing home regulations (OBRA '87) that discourage restraint use [26,27]. In the Netherlands, the secretary of state of the Ministry of Health, Welfare and Sports in 2009 has introduced a bill in Parliament ("Wet Zorg en Dwang") that regulates the use of physical restraints in people with dementia in general and belts in particular. According to this bill, the usage of belts to prevent falls will no longer be allowed [28]. The proposed changes in legislation provide an opportunity to develop a multi-component intervention tailored to the Dutch nursing home environment that will assist facilities in meeting this new requirement.

Among restraints used in Dutch nursing homes, belts are the most restrictive measure [4,19] therefore our intervention program, named EXBELT, primarily focuses on belt use reduction [25]. The EXBELT intervention includes four components: (1) promotion of institutional policy change that discourages belt restraint use, (2) education, (3) consultation by a nurse specialist, and (4) development and availability of alternative interventions. Cultural differences in staff opinions is an important consideration for the development of effective interventions. The educational component (including strategies for changing attitudes) for nursing home staff (physicians, nurses, paramedical staff and psychologist) is based on the intervention developed by Evans and colleagues [18] and Huizing and colleagues [19,23-25] that is customized for Dutch nursing home staff.

In 2007, EXBELT was developed and piloted in one nursing home ward [29]. The results of this pilot study were very promising. At baseline, 12 belts in 30 residents were used. After one month follow up, no belt was used, but after three and nine months follow up 1 belt was used. This reduction in belt use did not result in either an increase in the number of falls and related injuries or the use of other restrictive measures such as chairs with a locked tray table or psychoactive medication. Belts were replaced with, resident-centered interventions, such as movement and balance training, lower beds, hip protectors, extra supervision and monitoring devices (video camera, sensor mat, and infrared alarm systems). The recent expansion of the pilot (in 2008) to other wards in the same nursing home has shown similar results. However, this home does not represent a typical Dutch facility since it is considered as 'best practice' regarding restraint reduction initiatives and research. Thus, further testing of the EXBELT intervention is needed on wards in other nursing homes prior to widespread dissemination.

## Study aim and research questions

The first aim of this study is to further develop and test the effectiveness of a tailored multi-component intervention program (EXBELT) on belt restraint reduction in Dutch psychogeriatric nursing homes. However, the reduction of belts should not result in an increase of other restrictive restraints (such as a chair with locked tray table) or psychoactive drug use. The overall aim is an effective and feasible intervention that can be employed on a large scale in Dutch nursing homes. We translated the aims into the following eight specific research questions:

1. Does a tailored multi-component intervention (EXBELT) result in the reduction of belts in nursing homes?

2. Does EXBELT prevent the use of belts in newly admitted residents?

3. Does EXBELT reduce the use of other types of physical restraints?

4. Does belt elimination result in an increase of falls and fall related injuries?

5. What resident centered alternative interventions are used in EXBELT?

6. What is the opinion of nursing home staff, management and residents' relatives about EXBELT and the effectiveness of alternative interventions?

7. What are indicators for successful or unsuccessful implementation of EXBELT?

8. What improvements (related to content, organization and monitoring) are necessary to optimize the effect of EXBELT?

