## Methods/Design

### Design and sample

Effects of EXBELT will be studied in a quasi-experimental longitudinal study design. Alongside the effect evaluation, a process evaluation will be carried out in order to further develop EXBELT. Figure 1 shows the design of the study presented. After contacting seven Dutch nursing home associations (networks of nursing homes) in order to assess whether they would be interested to participate in our study, four nursing home associations, located in three regions in the Netherlands (Zuid-Limburg, Midden Limburg/Zuid-Oost Brabant en Zuid-Holland) contacted the EXBELT research group to participate in the current study. To participate, the prevalence of belt use on psychogeriatric nursing home wards had to be at least 10%. Wards are excluded if the unit is dedicated to residents with Korsakoff's, if far-reaching reorganizations and/or constructional renovations will be implemented, and if participating in other studies and/or projects aimed at the reduction of restrain use. The total study sample comprises four nursing home associations, 13 nursing homes with a total of 26 psychogeriatric wards. The 26 wards were assigned to either the intervention or control group. Assignment to either to intervention or control groups was carried out by the research team. Since no randomization took place, allocation was based on avoidance of contamination bias. Overlap of nursing home staff between the intervention and control wards was averted. In addition, based on the geographical location of the participating wards, wards from each of the four nursing associations that were situated closely together were allocated to the same group. The wards allocated to the control group will receive care as usual, while the wards allocated to the intervention group will receive the EXBELT program.

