### Sample size considerations

Sample size calculations are based on the primary outcome measure for residents: proportion of residents using a belt. We expect a reduction of 50% in belt use in the intervention group and no changes in use in the control group. Based on a significance level α of 0.05 (two sided) and a power of 60%, 216 residents are needed in each group in the analyses. Taken into account an informed consent rate of 80% and a drop-out rate of 25%, 720 psychogeriatric nursing home residents have to be selected at the start of the study.

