### Data analysis

Comparability between the intervention and control groups will be assessed at baseline to check for differences between the two groups on socio-demographic characteristics (age and gender). Outcomes at T2 and T3 will be compared between the intervention and control groups by both univariate and multivariate techniques. Data resulting from the effect evaluation will be primarily analyzed according to the intention-to-treat principle, i.e., including all participants with valid data, regardless of whether they remained in the setting which they were measured at baseline. Subsequently, the results of the intention-to-treat analysis will be compared with the results of a per-protocol analysis, to assess whether protocol deviations have caused bias. In all analyses effect estimates will be adjusted for baseline differences. Dropouts and losses-to-follow up will be described. Data resulting from the process evaluation will mainly be analyzed by means of descriptive techniques.

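### The falls question is about belt elimination, but the only comparison described covers all residents, most of whom wear no belt, so a null result would say little about harm after belt removal

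*Protocol article*

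**What the plan says.** The article's fourth research question (Study aim and research questions) is: "Does belt elimination result in an increase of falls and fall related injuries".

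Under Effect evaluation, falls and fall-related injuries come from the homes' fall registers for the three months before each measurement. Nothing restricts them to belted residents. Cognition, ADL and mobility, by contrast, are collected only in residents with a belt. Belt use itself is recorded for each resident at T1, T2 and T3.

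The Data analysis section states: "Outcomes at T2 and T3 will be compared between the intervention and control groups by both univariate and multivariate techniques". The primary analysis follows intention to treat and takes in every resident with usable data.

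Three other places bear on the size of the problem:
- Background: "Recent prevalence measures in the Netherlands have shown that 10% to 14% of nursing home residents are restrained with belts".
- Design and sample, as an entry condition: "the prevalence of belt use on psychogeriatric nursing home wards had to be at least 10"%.
- Sample size considerations: "We expect a reduction of 50% in belt use in the intervention group and no changes in use in the control group".

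The article gives no expected fall rate, no margin and no decision rule for falls.

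**The concern.** The question asks what happens to falls when belts are taken away. The residents most directly concerned are those wearing a belt at the start. The described comparison averages over everyone in each group, and on the prevalence figures in the article the belted residents are a small minority. A substantial harm in that minority would move the group-level fall rate only slightly.

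The Background reports that staff use restraints to prevent falls, and the overall aim is large-scale use of the programme. The answer to this question will therefore be read as the main safety evidence. An all-resident ratio close to 1 would be expected both when belt removal is harmless and when it doubles falls in those freed.

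**Working it through.** **The plan's own figures.** The selection target reproduces: 2 × 216 / 0.80 / 0.75 = 720. The article gives no baseline proportion behind the 216. At 60% power and two-sided α of 0.05, 14% against 7% with a continuity correction gives 216. Without the correction the result is 188 at 14%, 223 at 12% and 272 at 10%. So 216 is consistent with the top of the 10–14% range, although the article does not say that this was the input.

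**Inputs from the article.** Belt prevalence p = 10–14% (national, Background); at least 10% on participating wards (Design and sample); share of belts removed r = 0.5 (Sample size considerations) or r = 1 (the question's word is elimination, and the programme prohibits belts); n = 216 analysed per group.

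**Assumptions not in the article.** Falls double in freed residents. Belted residents otherwise fall q times as often as unbelted residents, with q = 1 in the main case. There are 0.3–0.8 falls per resident per three-month window. Counts are Poisson, without ward clustering.

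**Step 1: dilution.** The relative rise over all residents is p·r·q / (p·q + 1 − p). With q = 1 this is p·r.

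| Prevalence | Belts halved | Belts eliminated |
|---|---|---|
| 10% | 0.10 × 0.5 = 5%, RR 1.05 | 0.10 × 1 = 10%, RR 1.10 |
| 14% | 0.14 × 0.5 = 7%, RR 1.07 | 0.14 × 1 = 14%, RR 1.14 |
| 20% (illustrative) | 10%, RR 1.10 | 20%, RR 1.20 |

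Varying q from 0.5 to 2 at 10–14% prevalence gives a rise of 2.6–12.3% if belts are halved and 5.3–24.6% if they are eliminated.

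**Step 2: power of the all-resident contrast.** With λ falls per resident in the control group, SE(log RR) = √[1/(nλ) + 1/(nλ·RR)]. Power is Φ(log RR/SE − 1.96) + Φ(−log RR/SE − 1.96).

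- Lowest case (10%, halved, λ = 0.3): 64.8 against 68.0 expected falls, SE = 0.174, log 1.05 = 0.049, power 5.9%.
- Highest halved case (14%, λ = 0.8): 172.8 against 184.9 falls, SE = 0.106, log 1.07 = 0.068, power 9.8%.
- Belts eliminated: from 8.6% (10%, λ = 0.3) to 24.2% (14%, λ = 0.8).

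**Step 3: what a null result would exclude.** Take the most precise of these settings, λ = 0.8, and an all-resident estimate of exactly 1. SE = √(2/172.8) = 0.108, so the upper 95% limit is about 1.23. Solving 1 + p·r·(k − 1) = 1.23 for the ratio k in freed residents gives k = 1 + 0.23/0.07 = 4.3 (14%, halved) or 1 + 0.23/0.14 = 2.6 (14%, eliminated). Increases of that size would still be compatible with the data.

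**Step 4: residents belted at T1.** There are 216 × 0.10 = 21.6 to 216 × 0.14 = 30.2 per group. The rate ratio is 1 + r.

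| Scenario | RR | Power | 95% CI factor |
|---|---|---|---|
| Belts halved | 1.5 | 13–34% | ×/÷ 1.7–2.7 |
| Belts eliminated | 2.0 | 30–80% | ×/÷ 1.6–2.6 |

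Ward clustering would lower every power figure and widen every interval.

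**The case against.** The strongest counter-argument is that the all-resident contrast is a legitimate estimand. EXBELT is a ward policy. Residents unbelted at T1 who would later have been belted, and new admissions (the second research question), are exposed to it too. A comparison limited to residents belted at T1 misses harm in these groups. This stands: the all-resident comparison should stay, and it would be wrong to say that residents without a belt at T1 cannot be harmed.

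Second, this is a condensed article with one generic paragraph for all outcomes, and an analysis in belted residents may sit in the full protocol or SAP. This stands in part. An added subgroup may exist unseen, but the article does state which population is primary, and it restricts other measures to belted residents without doing so for falls.

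Third, the subgroup is small and its power is poor too. This is correct. The subgroup measures the relevant effect less diluted; it does not settle the safety question.

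Two stronger readings are tempting but unsupported:
- A reader might infer that the plan will declare no increase in falls from a non-significant test. The article states no such rule.
- A reader might take a 5–7% rise as the fixed consequence of the article's figures. It holds only if belts are halved, national prevalence applies to the study wards and q = 1. The wards have a floor of 10% and no ceiling. The pilot ward, in a home the article calls untypical, was far higher ("At baseline, 12 belts in 30 residents were used", or 40%).

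**Conclusion.** The concern holds in a limited form. The question is about belt elimination, and the only comparison described averages over all residents, most of whom have no belt to lose. If falls double in freed residents, the all-resident rate ratio at 10–14% prevalence is 1.05–1.07 with belts halved or 1.10–1.14 with belts eliminated. Power with 216 per group is then about 6–10% or 9–24%. These figures rest on equal underlying fall rates, an assumed 0.3–0.8 falls per window and no clustering. The dilution is milder at higher ward prevalence, for example a ratio of 1.10–1.20 at 20%.

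A null all-resident result would therefore say little about this research question. The all-resident comparison is not wrong; it answers a different question, the effect of the policy on a ward. What is needed is an inexpensive addition beside it.

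**What to change.** Keep the all-resident comparison and label it as the ward-level effect of EXBELT, including residents who would later have been belted. Add to the Data analysis section a pre-specified comparison of falls and fall-related injuries at T2 and T3 in residents with a belt at T1, intervention against control. Report it as a rate ratio with a 95% confidence interval that allows for ward clustering and adjusts for falls at T1. State that no conclusion of no increase will be drawn from the all-resident contrast alone.

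Defining the subgroup by belt status at T1 in both groups conditions only on a baseline variable. It avoids selecting residents by whether their belt was later removed.

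The cost is a sentence or two of text and no new data, since belt use and falls are already recorded in both groups. The downside is precision. With about 22–30 residents per group at 10–14% prevalence, the interval is at least ×/÷ 1.6–2.7 before clustering. It should be presented as an estimate of how much harm is excluded, not as proof of safety.

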## Methods/Design

### Design and sample

Effects of EXBELT will be studied in a quasi-experimental longitudinal study design. Alongside the effect evaluation, a process evaluation will be carried out in order to further develop EXBELT. Figure 1 shows the design of the study presented. After contacting seven Dutch nursing home associations (networks of nursing homes) in order to assess whether they would be interested to participate in our study, four nursing home associations, located in three regions in the Netherlands (Zuid-Limburg, Midden Limburg/Zuid-Oost Brabant en Zuid-Holland) contacted the EXBELT research group to participate in the current study. To participate, the prevalence of belt use on psychogeriatric nursing home wards had to be at least 10%. Wards are excluded if the unit is dedicated to residents with Korsakoff's, if far-reaching reorganizations and/or constructional renovations will be implemented, and if participating in other studies and/or projects aimed at the reduction of restrain use. The total study sample comprises four nursing home associations, 13 nursing homes with a total of 26 psychogeriatric wards. The 26 wards were assigned to either the intervention or control group. Assignment to either to intervention or control groups was carried out by the research team. Since no randomization took place, allocation was based on avoidance of contamination bias. Overlap of nursing home staff between the intervention and control wards was averted. In addition, based on the geographical location of the participating wards, wards from each of the four nursing associations that were situated closely together were allocated to the same group. The wards allocated to the control group will receive care as usual, while the wards allocated to the intervention group will receive the EXBELT program.

